## Abstract

**Background:**

Digital health tools can support behavior change and allow interventions to be scalable at a minimal cost. Keep-on-Keep-up Nutrition (KOKU-Nut) is a free, tablet-based app that focuses on increasing physical activity and improving the dietary intake of older adults based on UK guidelines. The intervention targets an important research area identified as a research priority reported by the James Lind Alliance priority setting partnership for malnutrition.

**Objective:**

This study aims to assess the feasibility of using the digital health tool KOKU-Nut among community-dwelling older adults to inform a future randomized controlled trial. The secondary aims are to determine the acceptability, usability, preliminary effect sizes, and safety of the study and the intervention (KOKU-Nut).

**Methods:**

This is a feasibility randomized controlled trial. We plan to recruit a total of 36 community-dwelling older adults using purposive sampling. Participants will be randomized 1:1 to either the intervention or the control group. The intervention group will be asked to engage with KOKU-Nut 3 times a week for 12 weeks. Participants in the control group will receive a leaflet promoting a healthy lifestyle. All study participants will complete questionnaires at baseline and the end of the 12 weeks. A sample of participants will be asked to participate in an optional interview. The study will collect a range of data including anthropometry (height and weight), dietary intake (3-day food diary), physical function (grip strength and 5-times sit-to-stand), perceived quality of life (EQ-5D), usability (System Usability Scale), and safety (adverse events).

**Results:**

Data collection commenced in March 2024, and the results will be ready for publication by January 2025. Feasibility will be determined on the basis of participants’ self-reported engagement with the intervention, and recruitment and retention rates and will be summarized descriptively. We will also consider the amount of missing data and assess how outcomes are related to group assignment. Acceptability will be measured using the modified treatment evaluation inventory and one-to-one semistructured interviews. Transcripts from the interviews will be analyzed using NVivo (version 12; QSR International) software using framework analysis to understand any barriers to the recruitment process, the suitability of the assessment measures, and the acceptability of the intervention and study design.

**Conclusions:**

The study aligns with guidelines developed by the Medical Research Council for developing a complex intervention by using qualitative and quantitative research to examine the barriers of the intervention and identify potential challenges around recruitment and retention. We anticipate that these results will inform the development of a future powered randomized controlled design trial to test the true effectiveness of KOKU-Nut.

**Trial Registration:**

ClinicalTrials.gov NCT05943366; https://classic.clinicaltrials.gov/ct2/show/NCT05943366

**International Registered Report Identifier (IRRID):**

PRR1-10.2196/50922

## Introduction

It is well established that progressive resistance training combined with strength and balance exercises are safe and effective for improving muscle mass, hip and lumbar spine bone mineral density, and muscle strength and function [1] and for reducing the risk of falls [2], hospitalizations, fractures [3], and mortality. Furthermore, diet has a fundamental role in the health of older adults [4], and meta-analyses have found that nutritional interventions in addition to physical activity lead to greater improvements in physical function, body composition, and strength in frail and pre-frail older adults [5-7].

Advancements in technology have provided the opportunity for digital platforms to remotely deliver, monitor, and complement patient care. Digital platforms can complement traditional face-to-face programs or provide an alternative option based on the individual’s preference and financial situation [8]. Furthermore, digital interventions can be scalable so they can maximize outreach at a minimum cost. Mobile apps are increasingly being used to support dietary change [9] and increase physical activity [10]; however, most are not designed for the older adult population. A recent systematic review identified that apps can be effective at increasing physical activity levels in community-dwelling older adults [8]; however, there has been little research investigating the effectiveness of apps to prevent malnutrition in this population [11].

Keep-on-Keep-up (KOKU) is a free, tablet-based gamified strength and balance exercise app that was soft launched in 2020 [12]. KOKU is approved by the National Health Service and Organization for the Review of Care and Health Apps as a lifestyle app and has been viewed positively by older adults after 6 weeks of independent use [13]. Anonymized Google analytics data show that there are more than 1000 users in the United Kingdom and users averaged 2.2 sessions per week, with an average weekly engagement of 1 hour 51 minutes. KOKU has a collection of health literacy games, and studies internationally found that engagement with the app led to increased exercise frequency and qualitative feedback found that the gamification was engaging and motivating [13]. Keep-on-Keep-up-Nutrition (KOKU-Nut) is a development of this gamification platform and includes an educational and interactive game based on the UK dietary guidelines to nudge older adults to improve their diet [14,15]. The game requires the user to choose a pair of cards to reveal food items, with the aim of finding matching food items. The user is presented with information about the different food items, and upon finding all the matching pairs, the user is provided with important tips to improve their diet and reduce their risk of malnutrition.

The intervention is based on qualitative work with 33 older adults to understand their determinants of dietary intake and barriers to healthy eating. Initial prototypes were tested on a diverse group of end users and health care professionals to facilitate co-design and ensure that the needs of the user were taken into consideration.

This study aims to assess the feasibility of conducting a randomized controlled trial (RCT) using KOKU-Nut to improve the dietary intake of community-dwelling older adults. The secondary aims are to determine the acceptability, usability, preliminary effect sizes, and safety of the study and the intervention (KOKU-Nut). These aims are in line with the Medical Research Council Framework that advocates conducting a feasibility study as part of the development and evaluation of complex interventions to assess the study design and the intervention itself [16].

## Methods

### Study Setting

This is a feasibility parallel group RCT study design using 1:1 randomization using both quantitative and qualitative methods to explore the feasibility and acceptability of KOKU-Nut (a digital service that aims to improve nutritional and fluid intake in community-dwelling older adults). Data will be collected from community-dwelling older adults living in Greater Manchester in the United Kingdom. The SPIRIT (Standard Protocol Items: Recommendations for Interventional Trials) statement and CONSORT (Consolidated Standards of Reporting Trials) statement extended to randomized pilot and feasibility trials and associated checklist were used in the design and reporting of this study [17,18] (Multimedia Appendix 1). Version 3 of the protocol was last updated on February 5, 2024.

### Eligibility Criteria

Participants will be included in the study if they are aged 65 years or older, living independently in the community, have access to the internet, and are willing to use an iPad or tablet (their own or one provided) for the duration of the study. Participants will be excluded if they are unable to communicate in English or have a known cognitive impairment.

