### Interventions

Participants in the intervention group will be helped to download KOKU-Nut onto their iPad or tablet during the baseline visit. The researcher (CF) will demonstrate the features and assist with any technical queries. In cases where participants do not have the necessary devices or data to join the intervention, a tablet with KOKU-Nut installed will be provided for the duration of the intervention. Participants will be asked to engage with KOKU-Nut at least 3 times a week throughout the 12-week period. This will involve carrying out strength and balance exercises and engaging with the gamification features relating to bone health and healthy eating. A crib sheet and contact details for the research team will be available if participants require additional support to help with technical issues.

Participants assigned to the control group will continue with usual care and receive a leaflet developed by Age UK about the importance of a healthy lifestyle including information on the importance of staying active and nutrition [19]. This will allow the comparison of a more traditional way to provide lifestyle advice compared to the digital health tool.

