### Outcomes

Primary outcomes will be related to feasibility and will assess engagement with the intervention, recruitment and retention rates, and acceptability of the intervention and study design. These findings are important to inform the development of a large-scale RCT in community-dwelling older adults to compare the effectiveness of KOKU-Nut to an information booklet about healthy living. Recruitment rates will be assessed as cumulative recruitment against the target rate each month. Retention rates will be calculated as the number of participants who completed the study divided by the number of participants randomized. Engagement with the intervention will be based on self-reported use of KOKU-Nut at the end of the 12 weeks (every day, 3-4 times a week, 1-2 times a week, and once or twice a month). A questionnaire previously developed and used by the research team for the KOKU app will assess the acceptability of KOKU-Nut [13]. Intervention acceptability will also be assessed using the 11-item, 7-point, modified Treatment Evaluation Inventory [20]. Higher scores indicate higher acceptability, with a score of 44 indicating moderate acceptability. Interviews will explore the acceptability of the intervention and the perceived impact of taking part in the study. Interviews will also consider the participant’s experience of the recruitment process, the assessment tools used, and their experience and motivation for participating in the study (positive and negative).

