### Recruitment

Men and women aged 65 years and older living independently in the community will be recruited through purposive sampling via local age UK groups, assisted living facilities, and university networks. We plan to recruit a mixture of participants with and without access to a tablet computer to explore differences in the outcomes and the experiences between those with and without prior experience with tablets or iPads.

The study will be advertised using social media, posters, and through current collaborations with sheltered housing facilities, local charities, and community-based organizations across Greater Manchester. Staff at assisted living facilities, charities, and community organizations will act as gatekeepers and will offer potential participants flyers about the study and participant information sheets. Older adults who are interested in participating can agree to have their details passed over to the research team (CF) and will complete the consent to contact form. The research team will follow up with participants who are interested in joining the study and screen potential participants. Alternatively, potential participants may contact the research team directly following the study advertisement in posters and on social media to find out more information and check their eligibility. An existing research database will also be used where older adults have previously consented to be contacted about future research. Participants on the research database will be contacted directly by the research team with the participant information sheet and summary of the research according to their preferred choice (via email, telephone, or letter). The research team will then arrange to conduct an initial telephone screening over the phone to determine eligibility, provide further information about the study, and answer any questions.

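### Eligibility does not exclude or record prior users or testers of the free KOKU app, and the described use scale cannot record non-use, so prior exposure and contamination could go unseen

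*Protocol article*

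**What the plan says.** Under Eligibility Criteria, the protocol article admits people aged 65 or older who live independently, have internet access and are willing to use a tablet. The exclusions are: "Participants will be excluded if they are unable to communicate in English or have a known cognitive impairment". Use of KOKU or KOKU-Nut is not mentioned.

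The Introduction says that KOKU "is a free, tablet-based gamified strength and balance exercise app that was soft launched in 2020", and that "Anonymized Google analytics data show that there are more than 1000 users in the United Kingdom". KOKU-Nut "is a development of this gamification platform and includes an educational and interactive game based on the UK dietary guidelines". The Abstract says that KOKU-Nut, too, "is a free, tablet-based app that focuses on increasing physical activity and improving the dietary intake of older adults". The Introduction adds that early prototypes were tried out by end users.

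Under Recruitment, participants come from Age UK groups, assisted living and sheltered housing, university networks and existing collaborations. In addition, "An existing research database will also be used where older adults have previously consented to be contacted about future research". Allocation stratifies by age group, gender and prior tablet or iPad experience.

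Under Interventions, "Participants assigned to the control group will continue with usual care and receive a leaflet developed by Age UK". Nothing is said about app use by controls. Under Outcomes, "Engagement with the intervention will be based on self-reported use of KOKU-Nut at the end of the 12 weeks", in four categories that run from daily use down to once or twice a month. Acceptability is measured partly with a questionnaire that the team used before for KOKU. Under Statistical Analysis, Cohen *d* is to be used to size a powered trial.

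**The concern.** The protocol treats familiarity with tablets as important enough to stratify on, but it does not deal with familiarity with the app itself. Two consequences are possible.

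- **App arm.** Someone who already uses KOKU, or helped to test a prototype, is not a newcomer to the intervention. Such people could report more engagement and higher usability and acceptability than the naive older adults a later trial would mostly enrol. Engagement and acceptability are primary outcomes. A former tester may also have answered the KOKU acceptability questionnaire before.
- **Control arm.** A control who uses KOKU, whether from before the trial or after hearing of the app through it, receives much of the exercise component. That could shrink the contrast from which the next trial is to be sized.

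Whether a free app can be tested under individual randomization is itself a feasibility question. The use measure described is framed as engagement with the intervention and has no category for non-use. It therefore cannot separate controls who never opened the app from controls who used it occasionally.

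**Working it through.** The plan gives no figure for prior use or contamination, so there is none to reproduce. The inputs from the document are 18 participants per arm, 1:1 allocation, 20% dropout and the planned use of Cohen *d*. The number of exposed people is an assumption throughout.

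**1. Could prior users enrol?** Let p be the share of prior users among recruits. The chance of at least one among n is 1 − (1 − p)^n.

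| Assumed p | Among 18 controls | Among all 36 |
|---|---|---|
| 0.1% | 1.8% | 3.5% |
| 1% | 17% | 30% |
| 5% | 60% | 84% |
| 10% | 85% | 98% |

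The user count is national and does not say which row applies.

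**2. Dilution of the contrast.** Let a share c of controls receive the full intervention effect. The observed effect is then d × (1 − c), and a sample size based on it is multiplied by 1/(1 − c)². The last column takes a true d of 0.5, two-sided alpha 0.05 and 80% power, all assumed.

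| Exposed controls of 18 | 1 − c | Fall in d | Multiplier of N | n per arm (63 undiluted) |
|---|---|---|---|---|
| 1 | 17/18 = 0.944 | 5.6% | 1.12 | 71 |
| 2 | 16/18 = 0.889 | 11.1% | 1.27 | 80 |
| 3 | 15/18 = 0.833 | 16.7% | 1.44 | 91 |

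Full exposure is an upper bound for someone using KOKU alone. KOKU shares the strength and balance content but not the new diet game, so its dilution would fall mainly on grip strength and sit-to-stand rather than on dietary intake.

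**3. Comparison with sampling error.** For d = 0.5 and 18 per arm, the standard error of d is √(2/18 + 0.25/(4 × 18)) = 0.339, and the 95% half-width is 1.96 × 0.339 = 0.66. With 20% dropout (14.4 per arm) the half-width is 0.74. The dilution in the table is 0.5 × 1/18 = 0.03 up to 0.5 × 3/18 = 0.08. It is far smaller than the sampling error, but it always runs in the same direction.

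**4. App arm.** Each prior user is 1/18 = 5.6 percentage points of any engagement proportion. That is the most one person can shift it, and only if without prior exposure that person would have counted the other way.

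**The case against.** The strongest objection is that much of this rests on silence in an article that condenses a fuller protocol. A reader might infer that controls are never asked about app use. The document does not say so. Under Data Collection Methods, everyone reports use of digital technology at baseline, baseline measures are repeated at 12 weeks, a follow-up case report file is completed, and some controls are interviewed. The file items are not shown, and the Outcomes section does not restrict the use question to one arm. This objection stands. What can be said is that no KOKU-specific item for controls is described and that the response scale, which is given, lacks a 'never' category.

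A reader might also infer that the results are biased. That is not supported either. No share of prior users or of exposed controls is given. The article does not say that the research database holds earlier KOKU participants. The 33 older adults named in the Introduction took part in qualitative work on diet, which is distinct from prototype testing.

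Third, the health outcomes are exploratory and no hypothesis test is at risk. If a free app counts as usual care, keeping its users is a defensible choice, and narrower eligibility costs some generalizability. This lowers the stakes and is a reason to accept recording as an alternative to exclusion. It does not justify leaving exposure unmeasured. The eligibility criteria are set out with just two exclusions, and they admit exposed people to both arms.

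**Conclusion.** The point holds as a gap in design and measurement, not as demonstrated bias. Current or former KOKU users and prototype testers are eligible for either arm, nothing described identifies them, and the use scale cannot record non-use in either arm. Engagement, usability and acceptability could be raised, and the contrast could be diluted, mainly for physical function.

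The size cannot be derived from the document. The reductions of 6% to 17% in d, and the 12% to 44% added to a future sample size, rest on the assumption that 1 to 3 of 18 controls receive the full effect. They are small beside the uncertainty of a trial this size, but systematic, and they would carry into the next trial's planning. The change is worth making because it is cheap and because it protects primary feasibility outcomes.

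**What to change.** - **Telephone screen.** Ask about current or previous use or testing of KOKU or KOKU-Nut. Either exclude such people or, at minimum, record the answer and report engagement, acceptability and effect sizes with and without them.
- **Twelve weeks.** Ask both arms how often they used KOKU or KOKU-Nut, with a 'never' option added to the scale. Report control-arm use as a feasibility (contamination) outcome.
- **No instruction to controls.** Telling controls not to install the app would suppress the very behaviour that the 12-week question is meant to measure.

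The cost is one screening question, one follow-up item and, if exclusion is chosen, one eligibility criterion. A few recruits may be lost, and naming the app at screening may draw some attention to it.

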### Interventions

Participants in the intervention group will be helped to download KOKU-Nut onto their iPad or tablet during the baseline visit. The researcher (CF) will demonstrate the features and assist with any technical queries. In cases where participants do not have the necessary devices or data to join the intervention, a tablet with KOKU-Nut installed will be provided for the duration of the intervention. Participants will be asked to engage with KOKU-Nut at least 3 times a week throughout the 12-week period. This will involve carrying out strength and balance exercises and engaging with the gamification features relating to bone health and healthy eating. A crib sheet and contact details for the research team will be available if participants require additional support to help with technical issues.

Participants assigned to the control group will continue with usual care and receive a leaflet developed by Age UK about the importance of a healthy lifestyle including information on the importance of staying active and nutrition [19]. This will allow the comparison of a more traditional way to provide lifestyle advice compared to the digital health tool.

### Outcomes

Primary outcomes will be related to feasibility and will assess engagement with the intervention, recruitment and retention rates, and acceptability of the intervention and study design. These findings are important to inform the development of a large-scale RCT in community-dwelling older adults to compare the effectiveness of KOKU-Nut to an information booklet about healthy living. Recruitment rates will be assessed as cumulative recruitment against the target rate each month. Retention rates will be calculated as the number of participants who completed the study divided by the number of participants randomized. Engagement with the intervention will be based on self-reported use of KOKU-Nut at the end of the 12 weeks (every day, 3-4 times a week, 1-2 times a week, and once or twice a month). A questionnaire previously developed and used by the research team for the KOKU app will assess the acceptability of KOKU-Nut [13]. Intervention acceptability will also be assessed using the 11-item, 7-point, modified Treatment Evaluation Inventory [20]. Higher scores indicate higher acceptability, with a score of 44 indicating moderate acceptability. Interviews will explore the acceptability of the intervention and the perceived impact of taking part in the study. Interviews will also consider the participant’s experience of the recruitment process, the assessment tools used, and their experience and motivation for participating in the study (positive and negative).

Secondary outcomes will consider the usability and safety of the intervention and the practicality of collecting and assessing the effectiveness of KOKU-Nut compared to an information booklet about healthy living. The perceived usability of KOKU-Nut will be assessed using the validated 10-item system usability scale. Responses are measured on a 5-point Likert scale ranging from 1 (strongly disagree) to 5 (strongly agree). A score >68 is considered above-average usability and >80 is considered high usability such that participants are likely to recommend the product to peers. The safety of the intervention will be based on the number of adverse events that occurred as a result of participation in the study. We will consider the practicality of collecting effectiveness data by documenting the amount and rationale for any missing data. Changes in means and SDs will be compared to consider the preliminary effectiveness of the intervention and to calculate sample sizes for a future trial. The study will be assessed against progression criteria based on Shanyinde et al [21] to determine progression to a powered RCT. Figure 1 shows the schedule of the intervention and assessment according to the SPIRIT statement.

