### Sample Size

As this is a feasibility study that is not designed to detect statistically significant differences in measures, no formal power calculation has been conducted to determine the sample size. Lancaster et al [22] recommend a sample size of 36 participants for feasibility and pilot studies, so after accounting for potential dropout (at 20%), we aim to recruit 18 participants in each arm.

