### Data Collection Methods

#### Overview

All participants will receive in the post a baseline case report file to be completed before the baseline assessment to collect sociodemographic information including age, gender, ethnicity, marital status, occupation, use of digital technology, shopping, and cooking habits. Participants will also be asked to complete a 3-day food diary using Intake24 prior to the baseline visit [25]. This web-based dietary assessment tool is compliant with the general data protection regulations (2018), and participants will be sent a unique number that will enable the researcher to identify the digital dietary records. Data collected will be used to assess the consumption of different food groups to identify adherence to the Eatwell guide [14]. During the home visit, the researcher (CF) will collect baseline measurements to assess anthropometry, dietary intake, physical function, quality of life, mood, and frailty. All measurements are responsive to change, appropriate for use in this population, and easily assessed in a community setting.

At the end of the 12-week intervention period, all baseline measures will be repeated, and participants will complete a follow-up case report file to collect feasibility outcome data. The researcher will conduct one-to-one semistructured interviews with a selected group of participants from both the intervention and the control group. Interviews will be conducted in person or over the phone depending on the preference of the participant. Interviews will last approximately 60 minutes, will be audio-recorded, and then transcribed verbatim by the research team. Additional consent will be collected prior to conducting the interview. A topic guide developed for the study will be used flexibly to guide the interviews.

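### The primary engagement item offers no answer for never using, stopping or less-than-monthly use of KOKU-Nut, and no denominator is stated, so a respondents-only figure would tend to overstate engagement

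*Protocol article*

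**What the plan says.** All references are to the protocol article.

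- **Outcomes** puts engagement first among the primary measures: "Primary outcomes will be related to feasibility and will assess engagement with the intervention, recruitment and retention rates".
- The same section defines it as use reported by the participant "at the end of the 12 weeks (every day, 3-4 times a week, 1-2 times a week, and once or twice a month". The list carries no 'for example' and reads as complete.
- **Interventions** sets the level of use requested: "Participants will be asked to engage with KOKU-Nut at least 3 times a week throughout the 12-week period".
- **Data Collection Methods, Overview** places the measurement at follow-up: "participants will complete a follow-up case report file to collect feasibility outcome data". No interim usage question, diary or app log is described for the trial.
- **Outcomes** defines retention over everyone randomised. It gives engagement no denominator.
- **Sample Size** gives the numbers: "after accounting for potential dropout (at 20%), we aim to recruit 18 participants in each arm".
- **Statistical Analysis** summarises engagement descriptively. It also plans to explore whether changes in health measures are associated with engagement.
- **Recruitment** plans to ask dropouts why they left. **Study Limitations** concedes recall bias in the self-reported feasibility measures.

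**The concern.** A feasibility trial of an app needs to be able to find out that people did not use it. The published scale cannot show this, because every available answer is a positive frequency. Someone who never opened the app, or gave up early, has no true answer.

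The timing adds a second problem. The item is answered once, at 12 weeks, so participants who drop out contribute nothing to it. With no stated denominator, the natural summary is a percentage of those who answered.

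Two later uses depend on this variable. Engagement is one of the feasibility indicators behind the decision on a powered trial, which Outcomes says will be judged against progression criteria. It is also an explanatory variable in the exploratory analysis. Non-users who are recorded as light users, or lost as blanks, would blur both.

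**Working it through.** The article states no engagement rate, threshold or precision, so there is no figure to reproduce. The check has three parts.

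**1. Do the four answers cover all possible use over 12 weeks?** Sessions = weekly frequency × 12. For monthly frequencies, 12 weeks is 12 × 12/52 = 2.77 months.

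| Use | Sessions in 12 weeks | Listed? |
|---|---|---|
| Every day | 7 × 12 = 84 | yes |
| 5-6 a week | 60 to 72 | no |
| 3-4 a week | 36 to 48 | yes |
| 1-2 a week | 12 to 24 | yes |
| About 3 a month | 3 × 2.77 = about 8 | no |
| Once or twice a month | 2.8 to 5.5, about 3 to 6 | yes |
| Less than monthly | fewer than about 3 | no |
| Never | 0 | no |

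Stopping part-way is ambiguous as well. Three times a week for 4 weeks and then nothing is 3 × 4 = 12 sessions, a mean of 12/12 = 1.0 a week. That participant could answer 3-4 a week (while active) or 1-2 a week (on average), or find no answer that fits current use.

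**2. What does the missing zero do?** There are two routes, with different effects.

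- *The never-user ticks the lowest answer.* Any use becomes 100%. With 1 never-user in 18 the truth is 17/18 = 94%; with 6 it is 12/18 = 67%. The share at 3 or more times a week does not change.
- *The never-user leaves a blank, and the blank is dropped.* The share at 3 or more a week rises. The numbers of never-users below, and the assumption that about 50% or 70% of users reach 3 a week, are mine; all 18 are taken to attend follow-up.

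| Never-users | Users reaching 3 a week | Over all 18 | Blanks dropped | Gap (points) |
|---|---|---|---|---|
| 1 | about 50% | 8/18 = 44.4% | 8/17 = 47.1% | 2.6 |
| 1 | about 70% | 12/18 = 66.7% | 12/17 = 70.6% | 3.9 |
| 3 | about 50% | 8/18 = 44.4% | 8/15 = 53.3% | 8.9 |
| 3 | about 70% | 10/18 = 55.6% | 10/15 = 66.7% | 11.1 |
| 6 | about 50% | 6/18 = 33.3% | 6/12 = 50.0% | 16.7 |
| 6 | about 70% | 8/18 = 44.4% | 8/12 = 66.7% | 22.2 |

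**3. What does dropout do, apart from the scale?** Inputs from Sample Size: 18 in the arm and 20% dropout, so 18 × 0.8 = 14.4, about 14 answering and 4 not. Assume 11 of the 14 report 3 or more a week.

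- Respondents only: 11/14 = 79% (Wilson 95% CI 52% to 92%).
- All randomised, the 4 non-responders taken as below 3 a week: 11/18 = 61% (39% to 80%).
- All randomised, the 4 taken as at or above 3 a week: 15/18 = 83%.

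The first two differ by 18 points. That difference would be the same with a perfect response scale, because dropouts do not answer either way. The third line shows that the direction depends on dropouts being lower users, which is plausible but not documented.

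**The case against.** The strongest reply has several parts.

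- *The form itself is not shown, and a condensed article may abbreviate the item.* Possible. But the article publishes these four answers as the scale of a primary outcome, without qualification.
- *The denominator of a descriptive percentage is often left to an analysis plan, and retention is reported beside engagement.* Fair. The missing denominator alone would not be a finding. It matters here because the item has no zero and is asked only at the end.
- *Non-engagement is not invisible: dropouts are asked for reasons, there are interviews and an acceptability questionnaire, and recall bias is admitted.* True, but none of these is described as recording a level of use, and the recall-bias caveat does not cover an answer that is absent.
- *Counting every blank as not engaged brings its own downward bias.* This stands. That figure should be labelled a conservative bound.

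A reader might also infer more than the documents support:

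- *That the item can only err upward.* It cannot be put that strongly. Someone at 5-6 times a week may choose 3-4, and someone at about 3 times a month may choose once or twice; both round down. Recall can err either way.
- *That the 5-6 gap distorts the share meeting the request.* It does not, because both neighbouring answers meet it.
- *That low or zero use is the expected case, because "users averaged 2.2 sessions per week".* The Introduction gives that figure for existing users of the earlier KOKU app, not for trial participants helped to install KOKU-Nut. An average among users says nothing about zero use.
- *That control participants could inflate engagement, because KOKU-Nut "is a free, tablet-based app".* Control-arm use is a separate contamination question and cannot raise the intervention arm's figure.

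**Conclusion.** The core point holds. As published, the primary engagement scale cannot record never using, stopping or less-than-monthly use. Any use is therefore 100% among those who answer, by construction. With no interim measure and no stated denominator, a respondents-only summary would tend to overstate engagement.

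The size cannot be derived from the documents, since it depends on how many participants never start or stop. Under the assumptions shown, dropping the blanks of 1 to 6 never-users adds about 3 to 22 points to the share at 3 or more times a week in an arm of 18. The 79% against 61% contrast is only an illustration of the dropout denominator. It would be wrong to read those 18 points as the effect of the missing answers, or to expect never-users who tick the lowest answer to add to them.

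This is a defect in how one descriptive primary outcome is recorded. No hypothesis test rests on it.

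**What to change.** 1. **Follow-up form.** Add 'never used', 'less than monthly' and 'stopped using in week __'. Close the gaps with an answer for 5-6 times a week and one that covers about 3 times a month.
2. **Analysis.** State that engagement is reported as the share using the app at least 3 times a week over all participants randomised to KOKU-Nut, with the respondents-only figure beside it. Show non-response as its own category, or count it as not engaged and label the result a conservative bound.

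Cost: one form item and one sentence. The Abstract reports that data collection has begun, so any follow-up already completed would lack the new answers, and the report should say how many. The denominator rule can still be set for everyone. The reported engagement may be lower.
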